### Denture construction

The Prosthodontic Research Team at LDI has developed and published a method of producing two or more sets of dentures which are clinically similar apart from the one deliberate alteration which is to be the subject of an RCT
[16]. This methodology will be used to produce two sets of dentures which are clinically similar apart from the impression material that was used to provide the mould for the fitting surface of each denture.

The intervention at the clinical secondary impression stage is the subject of this study; the secondary impressions will be made with either alginate or silicone. To take the secondary impressions, two sets of similar, spaced (2 mm), unperforated, light-cured acrylic secondary impression trays will be constructed. A set of impression trays consist of an upper and a lower tray; each set will be numbered in the laboratory A or B. Clinically, the secondary impression trays will be trimmed to size in the mouth to remove any over extension. After trimming, the trays will be randomly allocated to either the alginate or silicone impressions. The impression trays allocated to the alginate side of the study will be ‘border moulded’ with greenstick compound in the standard way
[17] and alginate (Xantalgin®) impressions taken. The trays allocated to silicone will be ‘border moulded’ with silicone (express 3 M) and impressions taken with silicone (express 3 M). The order in which the impressions are taken will be randomised; the patients will be rested for comfort for approximately 30 minutes between taking the first set of impressions and taking the second set of impressions. If a clinically adequate impression is not achieved at the first attempt with either material the impression will be repeated, until clinical adequacy is achieved. The total time taken to make the impression and number of attempts will be recorded.

Both sets of impressions will be immediately rinsed and disinfected using a proprietary disinfectant. After disinfection the alginate impressions will be wrapped in damp gauze and sealed in an airtight plastic bag; this is to comply with normal practice and the alginate manufacturer’s instructions. The silicone will be shaken dry and then placed in a plastic bag. The following day, both sets of impressions will be checked and cast with vacuum mixed dental stone. Once cast, the models produced will be thoroughly cleaned to remove all traces of alginate or silicone impression material. The models from the different impression materials will be permanently numbered by the Head of the Prosthodontic Research Laboratory (or an individual authorised to do so by the Chief Investigator) according to a randomisation schedule provided by the trial statistician. All dentists will be blind to which set of models came from which impression material.

In order to ensure similar dentures are constructed for both impression materials, the protocol for occlusal registration and wax trial insertion in the paper by Dillon et al
[16] will be followed. This protocol utilises silicone moulds of the occlusal and polished surfaces to shape and position teeth and surfaces of the duplicate denture. The dentures will be constructed with balanced occlusion and where possible given a balanced articulation on an average value articulator. Once construction of both sets of dentures is complete, the sets will be marked with a red or blue acrylic dot according to the sealed envelope containing the random allocation provided by the trial statistician, to randomise the order of wearing during the habituation period. Insertion and delivery of the completed dentures will proceed in the usual way.

### Habituation period (2 weeks)

Once dentures have been constructed, patients will be given both sets of dentures for a 2-week habituation period. The habituation period serves a dual purpose: firstly to allow patients to try both sets of unadjusted dentures to establish whether one set is preferred. Secondly, it has been suggested in a previous crossover study
[19] that patients tend to prefer the denture given in the second period because the first period is spent habituating to the feel of the new dentures which may feel very different to their old dentures. Thus by allowing a habituation period in this study it is hoped that patients will be used to the feel of the new dentures prior to the two adjustment study periods. During the 2 weeks the patients will be provided with a diary and asked to record the wearing of each set of dentures. Within the diary there is a randomised and structured programme alternating the use of the red and blue dentures with an opportunity for patients to provide qualitative feedback regarding the impact on behaviour and interactions in social settings wearing the new dentures. On the first day, they will be asked to wear the red denture; on the second day the blue denture. This initial period of alternation is to avoid familiarity and habituation clouding the later assessment. After 2 days they will be guided to wear the red-coded denture for 3 days followed by the blue-coded denture for 3 days. They will then be asked to frequently alternate the dentures for 2 days. Finally, for the last 4 days of the 2-week habituation period, they will be asked to wear whichever denture they prefer. On return to clinic they will be asked to report their preferred denture. If they have no preference they will be asked if this is because they were satisfied by both sets of dentures or if it is because both sets are unsatisfactory. They will then be asked to score each denture for comfort, mobility and chewing efficiency using a 5-point Likert scale and will complete a health economics questionnaire. Both sets of dentures will be returned and re-marked with a yellow or green spot by the Head of the Prosthodontic Research Laboratory (or designee).

### Adjustment period 1 (8 weeks)

The yellow set of dentures will be returned to the patient first. If any adjustment or remedial work is required to make the dentures comfortable, retentive and useful, this will be carried out by an experienced clinician. Within the limits of the LDI appointment system there will be no restriction on the number of appointments the patients can request during this 8 week period. Every appointment requested by the patient will be noted and a detailed record of the work required will be kept. The cost of any remedial treatment will be calculated. Although there is provision in this study for the adjustment of the dentures, it is expected that the majority of patients will require little adjustment. At the end of this first 8 weeks the patient will be asked to attend and report the impact the dentures have had on their quality of life by the completion of OHIP-EDENT and EQ-5D questionnaires and will rate the denture for comfort, mobility and chewing efficiency using 5-point Likert scales. Patients will also be asked to complete a health economics questionnaire.

The denture will be returned to the clinic and the green set of dentures given to the patient.

### Adjustment period 2 (8 weeks)

Any adjustments required for the second (green) set of dentures will be made and recorded as for Adjustment Period 1 (yellow). After 8 weeks the patient will return to clinic for a final assessment and asked to complete the OHIP–EDENT, EQ-5D and health economics questionnaires and will rate the denture for comfort, mobility and chewing efficiency. A sub set of patients will also be asked to think back to the two experiences they have had with the fitting/adjustment/wearing of the yellow (adjustment period 1) and then the green denture (adjustment period 2) and express any preference that they may have.

### Confirmation period (2 weeks)

After the two 8 week periods, it is to be expected that each set of dentures will be as good as it is possible to make them. The patient will be asked to take both sets of dentures away for a 2-week confirmation period. During this confirmation period the patient will be able to use whichever dentures they wish. They will be asked to return for a final visit to express any preference for the dentures and perform a Likert assessment of comfort, mobility, and chewing efficiency.

### Outcome measures

The co-primary outcome measures of the trial are patient expressed preference for unadjusted dentures and cost-effectiveness.

Secondary outcome measures are patient preference for adjusted dentures, patient assessment of comfort and taste (using a 5-point Likert scale) and preference of the impression materials, patient assessment of comfort, mobility, chewing efficiency of the dentures (using 5-point Likert scales).

Patient preference for dentures will be established by asking whether one or other denture is preferred, or whether there is no preference. Those expressing no preference will be further asked whether both dentures were satisfactory or unsatisfactory. Patients will be asked to reflect on the whole process of receiving the final denture (including initial comfort, amount of adjustment needed) when expressing preference for the adjusted denture.

Health-related quality of life will be measured using the OHIP-EDENT questionnaire
[18]. This questionnaire is adapted from the Oral Health Impact Profile (OHIP) and is particularly suitable for edentulous patients.

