### Randomisation and blinding

A series of randomisations and colour coding of the dentures will be introduced to ensure patients, dentists and dental nurses will be unaware of the impression material used to construct each set of dentures and the order of testing each denture made from each impression material. Dentures will be coded using a small coloured dot for identification – red or blue during the habituation period and green or yellow during the adjustment periods. It is likely that patients will form a preference for a particular set of dentures during the habituation period; dentures are re-coded after the habituation period in order that patients are unaware of which denture they are being given during the adjustment periods.

The Chief Investigator will carry out the clinical stages of denture construction up to and including the delivery of the dentures. The visits for the adjustment and assessment of the dentures will be conducted by an independent Consultant in Restorative Dentistry. The assessments of denture preference are patient reported.

Patients will undergo three randomisations (refer to Figure
1):

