### Assessments

Preference will be assessed for all patients at two time points during the trial. Patients will be asked to express a preference for the unadjusted dentures at the end of the habituation period, and preference for adjusted dentures at the end of the confirmation period. A sub set of patients will be asked to express a preference for the adjusted dentures at the end of the second adjustment period.

OHIP-EDENT and EQ-5D will be measured at baseline and at the end of adjustment periods 1 and 2.

A health economics assessment questionnaire will be completed at the end of the habituation period, and at the end of adjustment periods 1 and 2.

Assessment of comfort, taste and preference for the impression materials will be made immediately after both sets of impressions have been taken.

Assessment of Comfort, Mobility, and Chewing Efficiency will be assessed at the end of the habituation period, each adjustment period and the confirmation period.

A qualitative interview will be conducted on a subset of 18 patients in the course of scheduled visits when the dentures are being constructed and after the end of the confirmation period.

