## Discussion

Prosthodontic research has historically had a lack of RCT evidence
[8]. RCTs published in the prosthodontics literature have been reported poorly, lacking details regarding the details of randomisation and blinding which calls into question the quality of the studies themselves
[22]. This indictment of academic prosthodontics was a challenge for future researchers.

Carlsson looked at the lack of RCT evidence and went on to suggest that it is “not probable that comparisons between dentures made with varying materials and methods would lead to significant differences”. However the opinion of the authors is different; we believe the reasons for the lack of success with denture RCTs is the quality of protocol design coupled with twin problems within prosthodontics of multiple confounding variables and a sensitive meaningful outcome measure. The authors have accepted the challenge implied by Jokstad to design and execute a productive prosthodontic RCT protocol to CONSORT reporting standards. This paper gives full details of the protocol and the study for which it was designed.

This patient-centred study has been designed to address a key question in the construction of complete dentures, whether impression material has an impact on subsequent comfort and function of the constructed denture and whether that denture can be adjusted to the satisfaction of the patients. A crossover design has been used to eliminate many of the potentially confounding variables found in denture construction; patients are given 2 sets of dentures and act as their own control. This requires attention to the detail of the duplication techniques for the dentures
[16] to ensure the dentures are similar in all aspects apart from the impression material used at the secondary impression stage. In doing this, any preferences expressed can be reliably attributed to the impression material and not any other aspect of the denture construction. Additionally, a habituation period has been included in this study to guard against the potential for bias seen in other crossover studies
[9] that patients may prefer the denture they try in the second study period, a bias that has been attributed to the fact that the new dentures can feel very different to the patients existing dentures and the first study period is spent habituating to the new feel of the dentures

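### The outcome called preference for adjusted dentures is asked as a whole-process preference, so it cannot be read as a difference that remains after adjustment

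*Protocol article*

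**What the plan says.** All places are in the protocol article.

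- **Outcome measures** gives the outcome its status and label: "Secondary outcome measures are patient preference for adjusted dentures". The same section gives the instruction for answering: "Patients will be asked to reflect on the whole process of receiving the final denture (including initial comfort, amount of adjustment needed".
- **Assessments** separates two preference outcomes by time. The first is the co-primary: "Patients will be asked to express a preference for the unadjusted dentures at the end of the habituation period". The second is "preference for adjusted dentures at the end of the confirmation period".
- **Confirmation period** describes the dentures when the second question is put: "it is to be expected that each set of dentures will be as good as it is possible to make them". It describes the question only as expressing any preference and does not repeat the whole-process instruction.
- **Adjustment period 2** has a subset of patients "think back to the two experiences they have had with the fitting/adjustment/wearing of the yellow" set and then of the green set, and state any preference.
- **Discussion** names two parts of the key question. One is whether the impression material affects comfort and function. The other is "whether that denture can be adjusted to the satisfaction of the patients".

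**The concern.** The label and the timing point to a comparison of two finished dentures. The instruction points to the route by which each denture got there. The two elements it names, initial comfort and the amount of adjustment needed, do not describe the finished denture. A patient who finds the two sets equal at the confirmation visit, but remembers one as sore at first, is steered towards stating a preference.

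A reader of the results will naturally compare the unadjusted and the adjusted preference to see whether an effect of the impression material survives adjustment. With this wording, a difference that adjustment removed completely can still appear in the second outcome. Agreement between the two outcomes is then not independent evidence that the effect lasts. Because the components sit inside one answer, no later analysis can take them apart.

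**Working it through.** **1. The wordings side by side**

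| Section | When | What the patient is asked to judge |
|---|---|---|
| Adjustment period 2 | End of that period, subset only | Retrospective: fitting, adjustment and wearing of each set |
| Confirmation period | Final visit | Any preference, no basis stated |
| Outcome measures | Adjusted-denture preference | Whole process, including initial comfort and amount of adjustment |

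Two of the three are retrospective and the third is open. None confines the patient to the dentures as they are now.

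**2. The protocol's own figure**

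Inputs from Sample size: 60% v 30%, 10% no preference, 5% significance, 80% power, 76 patients. A two-sided test is assumed, as the article does not say. Let s be the discordant proportion, 0.60 + 0.30 = 0.90, and d the difference, 0.30.

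n = [1.96√s + 0.8416√(s − d²)]² / d² = [1.96 × 0.9487 + 0.8416 × 0.9]² / 0.09 = 76.1

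The stated 76 is reproduced, and 76/0.90 = 84.4, which rounds up to the stated 85. The sample size is not in question. The check shows that the illustration below uses the same test as the plan.

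**3. Illustration**

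Assumptions:
- Adjustment removes all difference, so true current-state preference is 45% v 45% with 10% none.
- 76 patients are evaluable.
- McNemar's test is uncorrected and two-sided. The article specifies McNemar for the unadjusted preference; its use for the adjusted preference is assumed.
- Among patients who state a preference, a share w answer from initial comfort, at the protocol's 60/30 split. The rest answer from the present state.

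The observed proportions are then 0.45 + 0.15w and 0.45 − 0.15w, so d = 0.30w and s stays at 0.90. The chance of rejection is approximately

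Φ[(d√76 − 1.96√0.90)/√(0.90 − d²)] + Φ[(−d√76 − 1.96√0.90)/√(0.90 − d²)]

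For w = 0.25, d = 0.075: Φ[(0.654 − 1.859)/0.946] + Φ[(−0.654 − 1.859)/0.946] = 0.101 + 0.004 = 0.105.

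For w = 0.5, d = 0.15: Φ[(1.308 − 1.859)/0.937] = 0.278, with a negligible second term.

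Full enumeration of the binomial probabilities gives:

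| w (assumed) | Apparent difference | P(reject) |
|---|---|---|
| 0 | 0 points | 0.05 |
| 0.1 | 3 points | 0.06 |
| 0.25 | 7.5 points | 0.105 |
| 0.5 | 15 points | 0.28 |
| 0.75 | 22.5 points | 0.55 |
| 1 | 30 points | 0.80 |

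The last row is simply the protocol's own power scenario and serves as a bound. It would need every patient with a preference to ignore the final denture, which the whole-process wording does not ask. With the exact McNemar test the values at w = 0, 0.25, 0.5 and 1 are 0.04, 0.09, 0.245 and 0.77, so the pattern is the same.

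**The case against.** The strongest reply is that this is an openly defined whole-process preference, apparently chosen on purpose, for a secondary outcome. No listed objective claims to isolate the preference left after adjustment, and the Discussion's phrase about adjusting to satisfaction can be read as an absolute question rather than a comparison of sets. The adjusted state is also measured without this instruction. Comfort, mobility and chewing are scored after each adjustment period and again, side by side, after confirmation. OHIP-EDENT is analysed at the end of each adjustment period.

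Most of that stands, and it limits the point. It does not remove the mismatch between label and question. The Discussion justifies preference as a sensitive and effective tool, so rating scales do not simply replace it.

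A reader might go further in four ways that the documents do not support:

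- *The item re-measures the unadjusted denture.* It asks about the whole process, after 16 weeks of adjustment periods and 2 weeks of free choice. The final denture is part of the answer.
- *Unequal recall biases the comparison of materials.* At the final visit the start of the yellow set is 8 + 8 + 2 = 18 weeks back and that of the green set 8 + 2 = 10 weeks. The order is randomised and balanced for habituation order, so the gap falls on both materials about equally.
- *The question invites patients to undo the re-coding.* Randomisation and blinding says that "dentures are re-coded after the habituation period in order that patients are unaware of which denture they are being given" in the adjustment periods, so a patient cannot simply repeat a red/blue choice by colour. Read with Adjustment period 2, initial comfort can mean the start of each adjustment period, and recalling that needs no unblinding.
- *Adjustment burden is merely counted twice, because the economic outcome costs it.* The cost of remedial work, primarily to the provider, is not the patient's experience of it.

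**Conclusion.** The point holds in a limited form. The outcome labelled preference for adjusted dentures is a composite of early comfort, adjustment burden and the final denture. A preference on it cannot be read as a difference that persists after adjustment. It would be too strong to infer that the trial as a whole cannot address the adjusted state, since the Likert and OHIP-EDENT data do. What is missing is a preference question confined to that state.

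The size depends on how many patients answer from early experience, which the documents do not give. If there is no residual difference and a quarter to a half of those with a preference do so at the 60/30 split, an adjusted-denture difference would be declared in about 10.5% to 28% of trials instead of 5%. These are false positives only if the outcome is read as its label suggests. Read as a whole-process preference, they reflect a real difference in experience. The co-primary unadjusted preference and the sample size are unaffected.

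**What to change.** - Reconcile the wording in Adjustment period 2, Confirmation period and Outcome measures.
- At the confirmation visit, ask first which set the patient prefers as the two fit and function now, and report that as preference for adjusted dentures.
- Then ask the whole-process question, and report it as a separate outcome under that name.
- For patients already assessed under the present wording, relabel the result as whole-process preference and do not interpret it as a difference remaining after adjustment.

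The cost is one extra question at a visit that patients already attend, and one extra reported outcome. Timing matters. Trial status gives 18 April 2012 as the date of last recruitment, so new wording may reach few patients. A mid-trial change would also leave two versions of the question, whose answers should be reported separately and not pooled. If too few patients remain for the new question to be useful, relabelling alone still prevents the misreading and costs nothing in data collection.

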### Assessments

Preference will be assessed for all patients at two time points during the trial. Patients will be asked to express a preference for the unadjusted dentures at the end of the habituation period, and preference for adjusted dentures at the end of the confirmation period. A sub set of patients will be asked to express a preference for the adjusted dentures at the end of the second adjustment period.

OHIP-EDENT and EQ-5D will be measured at baseline and at the end of adjustment periods 1 and 2.

A health economics assessment questionnaire will be completed at the end of the habituation period, and at the end of adjustment periods 1 and 2.

Assessment of comfort, taste and preference for the impression materials will be made immediately after both sets of impressions have been taken.

Assessment of Comfort, Mobility, and Chewing Efficiency will be assessed at the end of the habituation period, each adjustment period and the confirmation period.

A qualitative interview will be conducted on a subset of 18 patients in the course of scheduled visits when the dentures are being constructed and after the end of the confirmation period.

